##### MOC 2: Workplace intervention protocol

The workplace intervention consists of work(place) adaptations and is based on active participation and strong commitment of both the patient and employer. The workplace intervention is based on methods used in 'participatory ergonomics' [18-20]. Prior the start of the BRIDGE-study, three occupational therapists were trained by an expert to provide the workplace intervention protocol.

The process of the workplace intervention protocol is described in Table 1. The total duration of the intervention is eight hours, within 4 weeks. For each patient a team is formed that includes the occupational therapist (process mediator), the patient, the patient's supervisor, and other potential stakeholders (e.g. a Human Resources manager). Even in case the company itself has adjusted a workplace earlier, the occupational therapist makes an inventory of the workplace and the patient's tasks and informs the physical therapist and the care manager.

**Table 1 T1:** Steps of the workplace intervention protocol

**Step**	
0	Within 2 weeks after the patient visit the care manager, the OT makes by telephone an appointment with patient and patient's supervisor for the first visit of the workplace intervention protocol.
1	First visit consists of:
	1 Patient's workplace observation and inventory and ranking patient's tasks and obstacles for RTW by the patient.
	2 Inventory and ranking patient's tasks and obstacles for RTW by the patient's supervisor
	3 Patient, patient's supervisor and the OT brainstorm and discuss about as many solutions as possible to clear the obstacles for RTW.
2	Within two days after the OT has visited the workplace, the OT reports about all solutions and actions in a report to the patient, the patient's supervisor and the multidisciplinary team.
3	An optional worksite visit to give additional instructions or training to the patient will take place if necessary. The moment of execution depends on whether adjustments on the worksite have to be made first.
4	Four weeks after the first visit, an evaluation by telephone will take place between the patient and the OT with regard to the implementation of the solutions agreed upon. If necessary, a stakeholder has to be found for further support of improvements.
5	Within two days after the telephone evaluation, a final report is sent to the multidisciplinary team to report the progress of the protocol.

OT, occupational therapist; RTW, return to work.

The aim of the workplace intervention is to achieve consensus between patient and supervisor regarding feasible solutions for the obstacles for RTW. The solutions are judged on availability, feasibility and solving capability. After consensus, the occupational therapist, patient, patient's supervisor and potential other stakeholders agree on a plan of action. Responsibility for implementing the plan of action is put on the patient's and supervisor's account as much as possible.

##### MOC 3: The Graded Activity Program (GA)

This program is based on the principles of graded activity (GA) as developed by Lindström et al. [21,22] and on the operant (conditioning) model described by Fordyce [23]. It is adjusted to the Dutch situation in the study of Staal et al. 2004 [15]. The program used in this study has been adjusted to the particular study population of the BRIDGE-study. This GA program is provided by 10 regional physiotherapy practices located in Amsterdam or in the surrounding area. These practices have already been trained in the GA program in the context of other research projects [15,24,25]. Prior to the study, all physical therapist have followed a practical training course in the GA program (given by trainers) and were updated on the content of the BRIDGE-study.

The aim of the GA program is restoring occupational function and returning to previous work. Its aim is not pain reduction. The essence of the GA program is to implement an individually graded exercise program, which teaches the patient that it is safe to move while increasing the level of activity. During the GA program the patient has an active role in RTW and the physical therapist acts as a coach and supervisor, using a hands-off approach.

The GA program has two phases: 1. a baseline phase (pain/contingent); 2. a treatment phase (time/contingent). In Table 2 the content of the protocol is described. The entire program consists of maximally 26 sessions. The three baseline sessions have to be done in one week. The maximum duration is 12 weeks. However, the program stops as soon as a lasting return to own or equal work has been established. The session limit will not be communicated to the patient, because it will probably lead to a time lag regarding RTW.

**Table 2 T2:** Steps of the graded activity protocol

**Step**	**Characteristics**	
		The GA program starts within one week after the patient visits the care manager.

Before starting the baseline phase		-The PT performs a history-taking and a physical examination; -The PT gives counseling using the bio-psycho-social model on the development and maintenance and the consequences of pain; -The PT states that it is safe to start the GA program.

**1 Baseline phase**	**Pain Contingent** Patient may stop at any time if he feels pain or other discomfort Individual training 3 sessions of 1.5 hour	- Baseline consists of 6 fixed and 3 free exercises (simulating work situation); - Aim is to determine the maximal performance for each exercise separately; - According to the results, a start quota (70% of the mean) and the load of each exercise session until the end of the program will be set; - The load of each quota depends on the date of full RTW; - When all quota are set, the PT will send the baseline results and the treatment report to the employee, the employer and the multidisciplinary team.

**2 Treatment phase**	**Time contingent** Pain is not a reason for stopping or altering the program Group training twice a week (4–6 persons) 1 hour per session	- The pre-set quota have to be followed strictly; - The PT accompanies the treatment sessions and evaluates the sessions; - A positive reinforcement will be given by the PT after completion of the quota; - When the date of RTW is within a few weeks, the learned behaviour and management of pain will be discussed. At this point the frequency of the sessions will be decreased to once a week until the patient returns to work; - When the employee fully returns to work or after 26 sessions the protocol will stop. A final communication form will be send to the multidisciplinary team.

		Every three weeks, the PT sends an evaluation form to the multidisciplinary team to report the progress of the treatment protocol.

		When the patient is sick listed because of LBP within 4 weeks after RTW, the GA program will be continued. It will again stop as soon as the patient fully returns to work, or all 26 sessions of the GA program are given.

GA, graded activity; PT, physical therapist; RTW, return to work; LBP, low back pain.

##### 2. Usual clinical medical care (UC)

The patients who were allocated to the UC group receive the usual guidance by their medical specialist, occupational physician and general practitioner and allied health professionals. There are no specific requirements or restrictions with regard to type, duration or frequency of treatment. The patient's own general practitioner, occupational physician and treating medical specialist will be informed by letter about the study and the allocation of their patient to the UC group. They will be asked to adhere to their professional guidelines for LBP (if available) [1,3,4].

### Outcome assessment and data-collection

#### 1. Quantitative outcome assessment

Most of the outcome variables, are reported by means of self-reported questionnaires and will be assessed four times by all participants: before randomization (T0), at the end of 3 months (T1), at the end of 6 months (T2) and 12 months after randomization (T4). Prognostic outcomes are assessed at T = 0. The direct and indirect medical costs are measured four times by means of cost diaries. This cost diary is inserted into the questionnaire at 3, 6, and 12 months after randomization and is sent at 9 months after randomization separately to the participant. For the outcome RTW, sick leave data are gathered by mailing a calendar monthly and are checked with the data records of the occupational health services after 12 months. Patients are reminded by telephone after two weeks if they have not returned the questionnaire, the cost diaries or the calendar yet. Table 3 presents the outcome variables, the used instruments and the timing of the data collection.

**Table 3 T3:** Overview of variables measured in this study

Variable	Time Measured				
	Baseline T0	3 months	6 months	9 months	12 months
		T1	T2	T3	T4

Inclusion/exclusion	x				
Informed consent	x				
Randomization	x				
Prognostic variable					
Demographic variables (age, gender, ect)	x				
Potentional work-related physical factors (DMQ)	x				
Potential work-related psychosocial factors (JCQ)	x				
Outcome measures					
Primary					
Return to work	x	x	x		x
Secondary					
Pain intensity (VAS)	x	x	x		x
Functional status (RDQ-24)	x	x	x		x
Pain coping (PCI)	x	x	x		x
Quality of life (Euroqol)	x	x	x		x
Patient Satisfaction with Occupational Health Services (PSOHSQ)		x			
Cost diaries		x	x	x	x

#### 2. Qualitative outcome assessment

Outcome variables related to the implementation of the protocol will be gathered by 1. additional questions about the multidisciplinary outpatient care program for patients in the multidisciplinary outpatient care (MOC) group, which are inserted into the questionnaire at T1; 2. an in-depth interview about the multidisciplinary outpatient care program with the first 30 patients randomized to the MOC group, which is done by telephone at T1. The interview will take approximately one hour; 3. questionnaires, sent to the stakeholders involved (employer/supervisor, patient's own GP and OP, professionals of the multidisciplinary team) at T1; 4. two focus groups for 5 to 7 professionals of the multidisciplinary team (care manager, physical therapist, occupational therapist and medical specialist) organized during the first year of recruitment of patients.

### Outcome measures

#### Primary outcome

The primary outcome is RTW defined as: "duration of sick leave in calendar days from the day of randomization until full RTW in own or other work with equal earnings, for at least 4 weeks without (partial or full) recurrence. In addition, the total duration of sick leave due to LBP (including all recurrences of sick leave episodes due to LBP) will be calculated for the entire follow-up period. Patients are asked monthly 1. to register the percentage of sick leave i.e. dividing the number of hours a patient is sick listed by the number of hours of the patients working week multiplying with a 100%; 2. the reason for being on sick leave, i.e. LBP, influenza ect. After a patient has been followed for a period of 12 months, a letter will be sent to the patient's occupational physician with the request to provide the sick leave data of the last 12 months registered in the data records of the occupational health services. Because some patients are self-employed, the self-reported data will be used for statistics.

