#### Participants

The population consists of LBP patients (18–65 years) who visit an outpatient clinic (mainly orthopaedics and neurology, but also rheumatology and neurosurgery) of one of the participating hospitals. The population has to 1. have LBP lasting more than 12 weeks, 2. have paid work (i.e. paid-employment or self-employed) for at least 8 hours a week and 3. be on (partially) sick leave. Patients will be excluded from the study in case of 1) being sick listed more than two years; 2) working temporarily for an employment agency without detachment; 3) having specific low back pain, due to infection, tumor, osteoporosis, rheumatoid arthritis, fracture or inflammatory process; 4) having had a lumbar spine surgery in the last 6 weeks or having to undergo surgery or invasive examinations in the near future (within 3 months); 5) having serious psychiatric disorders; 6) having cardiovascular or medical contraindications for physical activity according to the Physical Activities Readiness Questionnaire (PAR-Q) [16]; 7) being pregnant or having given birth in the last 3 months; 8) dealing with a lawsuit to their employer; 9) not having the ability to complete questionnaires written in the Dutch language.

In order to recruit a sufficient number of eligible patients, in each hospital a competent hospital employee will identify the source population weekly from the computerized patient record system. Within one week after the visit, the patients will receive three documents by mail: 1. a letter from their medical specialist in which they are informed about the study and asked if they are willing to participate, 2. a brochure with details of the study and 3. a short screening questionnaire. A return envelope is enclosed for returning the screening questionnaire to the researcher. On this questionnaire they can indicate if they are willing to participate in the study.

All patients who return the questionnaire, meet the criteria and indicate that they are willing to participate will be contacted by telephone. The researcher or a research assistant will provide additional information about the implications of participation and will check the eligibility of the patient. If a patient meets the selection criteria and is willing to participate, they will be asked to sign the informed consent.

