#### Secondary outcomes

- Pain intensity is measured by three short questions using a 10-point Visual Analogue Scale (VAS) [26].

- Functional status is assessed by the Roland-Morris Disability-24 Questionnaire (RDQ-24), which has shown to be useful in LBP research [27,28].

- Pain coping is measured with the Pain Coping Inventory Scale (PCI) [29].

- Quality of life is measured with the Dutch translation of the Euroqol instrument [30].

- Cost diaries are used to measure direct (non)-medical costs. The cost diary includes direct health care costs relevant to the treatment of LBP, such as visits to a general practitioner, occupational physician, manual therapist, physical therapist, other exercise therapy or complementary health therapists (e.g. acupuncturist), visits to a medical specialist in orthopaedic surgery, neurology, rheumatology, or rehabilitation medicine, and hospitalization. Direct non-health care costs include homecare and costs for paid and unpaid help due to the disability.

- A process evaluation will be conducted after implementation of the protocol and inclusion of the first 40 cases treated with the multidisciplinary outpatient care program. Quantitative and qualitative data about the applicability, compliance, satisfaction and barriers related to the (implementation of the) protocol will be collected. Patient satisfaction will be measured with the Patient Satisfaction with Occupational Health Services Questionnaire (PSOHQ)[31].

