### Blinding

Patients, therapists and researchers cannot be blinded for the allocated treatment. Treatment allocation takes place after informed consent and completion of the baseline questionnaire. Most outcome measures are self-reported and consequently cannot be blinded. However, since all questionnaires are sent to the patient by mail, researcher and care providers are not likely to influence the way patients complete the questionnaires. In addition, the reliability regarding the self-reported data on RTW is checked by sick leave data derived from databases of occupational health services. The therapists of the multidisciplinary team (care manager, occupational therapist, physical therapist) are not involved in assessing any of the outcomes.

After randomization all patients receive their own code. A run-up number and the first two letters of the visited hospital compose this code. The research assistant will put all data in the computer by code. Therefore, the analysis of the data by the researcher will be blind.

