### Economic evaluation

Cost-effectiveness will be evaluated from the societal perspective including both direct and indirect costs. Both costs groups will be estimated according to the Dutch guidelines for cost analysis in health care research [38,39] or with the use of the tariffs of the Dutch Central Organization for Health Care Charges [40]. These costs will be measured 4 times during the one-year follow-up. Indirect costs of loss of production due to LBP are not related to health care, but are costs in paid and unpaid labour as a consequence of sickness, sick leave, disability and/or death of a productive person. Mailing the patient monthly a calendar as well as collecting the sick leave data collected in occupational health services database will measure the number of days on sick leave due to LBP. Quality of life will be measured according to the standard Dutch version of the EuroQol [30]. Costs will be summated for each individual patient. Bootstrapping will be used for pair-wise comparison of the mean groups to calculate mean differences in direct, indirect and total costs between the two groups of patients. Confidence intervals (95%) will be obtained by bias corrected and accelerated bootstrapping. A cost-effectiveness ratio will be calculated by dividing the difference between the mean costs of the intervention groups by the difference in RTW between the intervention groups. A cost-utility analysis will also be conducted in which the incremental costs per QALY will be estimated. Reliability of the cost-effectiveness ratios will be graphically presented on a cost-effectiveness plane and acceptability curves.

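### Total sick leave and productivity costs count only days the unblinded patient attributes to low back pain, so any between-arm difference in other absence stays outside these results, although the calendar records it

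*Protocol article*

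**What the plan says.** All references are to the Protocol article.

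- **Primary outcome.** The main outcome is time from randomization to full, sustained RTW. A second measure follows: "the total duration of sick leave due to LBP (including all recurrences of sick leave episodes due to LBP) will be calculated" for all of follow-up. Each month patients are asked "to register the percentage of sick leave" and to give "the reason for being on sick leave, i.e. LBP, influenza ect". Occupational health records are requested after 12 months, but "the self-reported data will be used for statistics".
- **Economic evaluation.** The perspective is societal. For productivity loss, the calendar and the occupational health database "will measure the number of days on sick leave due to LBP".
- **Secondary outcomes.** On direct costs: "The cost diary includes direct health care costs relevant to the treatment of LBP".
- **Blinding.** "Patients, therapists and researchers cannot be blinded for the allocated treatment".

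The calendar therefore captures absence of any cause, with its reason. The stated analyses of total duration and of productivity cost use only the part labelled LBP.

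**The concern.** A cause-restricted total compares the arms fairly only if absence for other causes, and the way patients label absence, are the same in both arms. The design gives some reason not to take that for granted. One arm receives a supervised exercise program and is steered towards earlier RTW. The exclusion for "having cardiovascular or medical contraindications for physical activity according to the Physical Activities Readiness Questionnaire (PAR-Q") shows that the authors recognise exercise risk outside the back. The label also has a consequence in one arm only: under Table 2, a patient in the multidisciplinary outpatient care (MOC) arm who is sick listed again for LBP within 4 weeks of RTW continues the graded activity program.

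Non-LBP absence could differ between arms through injury in another body region, other illness after return, or relabelling of the reason. Any such difference would be missing from total sick leave and from productivity costs. A conclusion that the program saves sick leave, or is cost-effective for society, could then say more than the data show, or less.

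**Working it through.** The plan gives no figure on this point to reproduce, and the sample size does not depend on it. The check is an identity followed by a scale.

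**1. Identity.** For each arm let L be mean LBP sick-leave days over 12 months and N mean non-LBP days. UC is usual care.

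- LBP-only saving: S = L(UC) − L(MOC)
- Excess non-LBP days in the MOC arm: d = N(MOC) − N(UC)
- All-cause saving: [L(UC) + N(UC)] − [L(MOC) + N(MOC)] = S − d

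The LBP-only total differs from the all-cause total by exactly d. If d = 0 they agree. If d > 0 the LBP-only figure overstates the all-cause saving; if d < 0 it understates it. Absence relabelled from LBP to another cause in the MOC arm raises S and d equally and leaves S − d unchanged, so the all-cause total is immune to labelling.

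**2. Scale.** The documents give no rate of non-LBP absence, so d is an assumption. The only day figures for S are the 29 to 105 days that the section on the study's impact cites from primary care. They serve here as a yardstick, not as this trial's expected effect.

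| Assumed d (days per patient) | All-cause saving if S = 29 | All-cause saving if S = 105 |
|---|---|---|
| +20 | 29 − 20 = 9 | 105 − 20 = 85 |
| +5 | 29 − 5 = 24 | 105 − 5 = 100 |
| 0 | 29 | 105 |
| −5 | 29 + 5 = 34 | 105 + 5 = 110 |
| −20 | 29 + 20 = 49 | 105 + 20 = 125 |

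Relative to S, an imbalance of 5 to 20 days is 5/105 = 5% to 20/29 = 69%, in either direction.

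**3. Costs.** With a price p per day, the LBP-only productivity saving is p × S and the all-cause saving is p × (S − d), so the gap is p × d. The article gives no p, so no euro amount follows. Productivity loss enters the numerator of both planned ratios. Neither effect measure is tied to LBP as written: RTW names no cause, and the QALY rests on EuroQol, a generic instrument. Each ratio would therefore set an effect open to any cause against LBP-only costs.

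**4. What is not affected.** The definition of the primary outcome requires at least 4 weeks without recurrence and names no cause, and Data analysis adds no LBP limit. EuroQol can register ill health from any cause. Worsened back pain still counts as LBP leave and LBP cost, and can show in the pain scale and the RDQ-24.

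**The case against.** **A condition-specific total is legitimate.** It removes influenza and other unrelated absence and gains precision. This stands: the LBP-only total need not be dropped. It does not settle the productivity costs under a societal perspective, where a lost day costs the same whatever its label.

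**Occupational health records check the self-report.** This stands in part. The check is described for RTW, the article does not say whether the records hold a cause, the self-employed are said to lack access to occupational health care, and self-report is what is analysed. The records do not show that attribution is protected.

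**A condensed article may leave sensitivity analyses to a fuller document.** True, and an all-cause analysis may be planned there. But the LBP restriction is a stated choice, made for total sick leave, productivity loss and the cost diary alike, so the point does not rest on silence.

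**A stronger reading is tempting.** A reader might infer that harm from the exercise program or from early return drops out of the results altogether, or that the restriction always favours the program. The documents support neither. Back-related harm is counted; harm of any cause can delay or break sustained RTW under the primary definition and can lower EuroQol. The direction depends on the sign of d. Usual care is unrestricted, may itself include exercise therapy, and has its own non-LBP absence. A magnitude that assumes non-LBP absence in the program arm and sets usual care to zero would be invented.

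**Conclusion.** The point holds for two results: total sick leave over follow-up, and productivity costs with the cost-effectiveness results built on them. Both rest on a cause given by an unblinded patient. Both leave out the between-arm difference in non-LBP days, and no stated analysis would reveal it. The size is d days per patient, with d unknown in sign and amount and possibly zero; the range of 5 to 20 days in either direction is assumed for illustration only. The primary RTW analysis is not undermined, nor are EuroQol, pain or RDQ-24. This is a cheap improvement, not an error that invalidates the trial.

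**What to change.** Keep the LBP-only measures and add the following, pre-specified as a sensitivity analysis from calendar data already collected:

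1. All-cause sick-leave days over 12 months by arm, with the difference and its interval, beside the LBP-only total.
2. The productivity-cost and cost-effectiveness results repeated with all-cause days.
3. A table of non-LBP absence by recorded reason and arm.
4. A reporting rule: if the two versions disagree, describe the total-sick-leave and societal cost results as LBP-specific.

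The cost is one repeated analysis, some coding of recorded reasons and one table. There is no new data collection and no change in sample size or care. The downside is that all-cause days carry unrelated absence, so the estimates are noisier and the intervals wider; a wide interval alone should not be read as disagreement. The calendar cannot supply direct care outside LBP treatment, so that restriction in the cost diary would remain and should be stated as a limit of the societal perspective.
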